# A comparison of the effects of occupation-based interventions with and without responsibility feedback and conventional interventions on participation in people with idiopathic Parkinson’s disease: study protocol for a randomized controlled trial

**DOI:** 10.1186/s13063-023-07526-3

**Published:** 2023-09-26

**Keywords:** Occupations, Occupational therapy, Parkinson’s disease, Participation, Rehabilitation

## Abstract

**Background:**

Parkinson’s disease (PD) is a neurodegenerative disorder with debilitating motor and non-motor symptoms which affect participation in meaningful occupations. Occupation-based interventions can improve participation in people with PD. Evidence for incorporating structured and intensive occupational therapy by considering the concept of responsibility is lacking for this population. This trial will compare the effects of occupation-based interventions with and without responsibility feedback and conventional interventions on participation in people with idiopathic PD.

**Methods:**

A total of 45 people with PD, between 35 and 85 years old and Hoehn and Yahr stages between I to III, will be recruited from movement disorder centers for this three-armed study. Participants will be randomized into three groups (occupation-based interventions with responsibility feedback, occupation-based interventions without responsibility feedback, and conventional interventions). All participants will receive intervention for 24 sessions during a period of 12 weeks (2 sessions per week). The primary outcome measure will be participation satisfaction. Participation frequency and restriction, self-perceived performance, performance satisfaction, motivation, volition, sense of agency, responsibility, physical activity, community integration, activities of daily living (ADL), instrumental ADL, upper extremity function, balance, fatigue, and quality of life will be measured as secondary outcome measures. All outcomes will be measured at baseline, session 9, session 17, post-intervention (week 13), and follow-up (week 25).

**Discussion:**

This home-based high-intensity, structured, client-centered, and occupation-based intervention will be conducted by utilizing the concept of responsibility. This proposed trial may result in enhanced participation that would benefit other motor and non-motor symptoms in people living with PD. Findings from this proposed study are expected to expand the knowledge of clinicians and help them in evidence-based decision-making processes.

**Trial registration:**

Iranian Registry of Clinical Trials IRCT20140304016830N13. Registered on August 19, 2022

**Supplementary Information:**

The online version contains supplementary material available at 10.1186/s13063-023-07526-3.

## Background

Parkinson’s disease (PD) is recognized with debilitating motor and non-motor symptoms [1, 2]. Non-motor complications lead to the limitations in activities of daily living (ADL), restricted participation in meaningful occupations, and decreased quality of life [3–5].

Reduced basal ganglia output in PD plays a critical role in motivation [6, 7] and volition [8] brain circuits. The literature proposed that the relation between motivation and volition affects participation [9–11]. Participation in occupations includes motivational (i.e., pre-decisional and post-actional) and volitional (i.e., pre-actional and action) processes [10, 12]. Motivational and volitional levels are prerequisites for participation and adherence to therapeutic interventions [13]. Occupational therapy (OT) with a client-centered and occupation-based approach can address these issues [14, 15].

Based on the literature, a sense of responsibility affects motivation, volition, and ultimately participation [8, 16, 17]. People living with chronic diseases (e.g., PD) tend to lose their sense of responsibility towards their daily occupations and feel incapable of managing their lives [18, 19]. Hence, interventions based on this concept may be beneficial for increasing motivation, volition, and participation.

Over the past two decades, most intervention studies for this population were multidisciplinary (including OT) [20–24]. Only two recent large-scale studies were conducted with a client-centered approach [25, 26]. Sturkenboom et al. [25] compared the efficacy of home-based OT in Parkinson’s disease (OTiP) with usual care (no OT) over a 10-week program (average of 8 1-h sessions). Self-perceived performance and satisfaction in daily activities were improved but participation did not benefit from this intervention. Clarke et al. [26] delivered low-dose (i.e., median 4 1-h sessions in 8 weeks) individualized physiotherapy and OT in mild to moderate PD and concluded no immediate or medium clinically meaningful improvements in ADL or quality of life. They concluded that low-dose therapy in early PD stages is ineffective and suggested more structured and intensive programs. A recent systematic review [27] indicated that drawing rigorous conclusions on OT intervention approaches is currently impossible. Literature recommended that upper extremity and ADL functioning should be addressed simultaneously with high-intensity programs. Also, this study suggested that non-motor symptoms require further attention.

The concept of sense of responsibility was not considered in the aforementioned studies while delivering interventions. Sense of responsibility refers to the intentional binding mechanism that connects our intentions to the corresponding outcomes. We attribute our own activities to ourselves in this process; hence, we feel a sense of control and accountability [28, 29]. Sense of responsibility is intertwined with agency (i.e., controlling doing of occupations and their consequences) and its neural correlates. These neural correlates (e.g., angular gyrus, insula, supplementary motor area) play a critical role in agency and responsibility [30, 31]. Sense of responsibility and agency are crucial while executing goal-directed occupations [32–34] and may change health-related behaviors, such as non-motor symptoms [35, 36]. Moreover, feedback (knowledge of result or knowledge of performance) may cause behavioral and neurological changes and hence promote participation [37]. This study aims to conduct a trial to compare the efficacy of occupation-based interventions on participation in people living with idiopathic PD in three groups: (1) occupation-based interventions with responsibility feedback, (2) occupation-based interventions without responsibility feedback, and (3) conventional interventions.

## Methods

### Trial design

A parallel, three-armed, double-blinded (assessor and patients) randomized controlled trial will be conducted. Individuals will be assigned to each group in a ratio of 1:1:1 (group A: occupation-based interventions with responsibility feedback; group B: occupation-based interventions without responsibility feedback; group C: conventional interventions). The CONSORT diagram [38] will present the trial design (i.e., enrollment, allocation, and assessments) in brief (Fig. 1). This clinical trial follows the recommendations for Interventional Trials (SPIRIT) [39] statements (Additional file 1).

**Fig. 1 Fig1:**
[figure not shown]
Flow diagram illustrating trial design for people with idiopathic Parkinson’s disease

### Participants and recruitment procedures

Community-dwelling individuals with Parkinson’s will be recruited from movement disorder centers and rehabilitation clinics in Tehran, Iran. Advertisements in Iran’s Parkinson Association will be done. Individuals who meet the inclusion criteria (see section below) will receive consent form and information regarding study aims and procedures.

Due to COVID-19 pandemic precautions, patients will only come to the OT clinic for evaluations. All sessions will be free for participants, and travel costs for evaluation will be paid by the research team. Both assessments and interventions will be conducted in the “ON” (1 h after levodopa intake) medication state. Levodopa equivalent dose (LED) will be calculated for individuals in each assessment session using Tomlinson et al. formula [40].

### Data collection

The assessor (an occupational therapist with 6 years of experience in neurological rehabilitation) will conduct initial screening and outcome measure evaluations at baseline, session 9, session 17, post-intervention (week 13), and follow-up (week 25) (Table 1). Since this is a low-risk study, independent data monitoring and auditing will not be taken into consideration. Written feedback about the results of the evaluations will be provided to all participants in order to promote retention. A recent systematic review suggested that people with PD will benefit from moderate to high doses of intervention (≥ 8 sessions and ≥ 10 weeks) [5]. We will intend to discover the proper dose of intervention by multiple assessments during the treatment process. Treatment sessions will be started 1 or 2 days after the initial screening in participant’s homes for 12 weeks (two times a week) by three experienced occupational therapists (average 5 years of experience). The occupational therapists will be trained for 2 days regarding the study procedures and intervention protocols. Therapists will be allowed to contact the main researcher to share any issues that arisen in the intervention process. Home-based therapy with a focus on meaningful occupations appears to be the most plausible beneficial intervention [27]. Moreover, the environment is more familiar for the patient, and near-ones find it more convenient [41].

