### Interventions

First, the importance of therapy in people with PD will be explained to participants. In each group, treatment sessions will be delivered two times a week (Sunday/Tuesday, Saturday/Wednesday, or Monday/Thursday) for 12 weeks. Each session will be approximately 60 to 90 min. Treatment sessions will be performed in the morning or evening based on the participant’s convenience and medication regime (i.e., being in “ON” state while receiving treatment). Rest will be provided for each patient as required. Participants will be instructed not to receive any other types of rehabilitation intervention during the treatment sessions. Moreover, the intervention will be discontinued when participants express their desire to terminate the intervention.

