The functional level of each patient will be determined using the Gentile taxonomy. The intervention will be delivered to patients at any level of the taxonomy where they experience challenges. Participants will receive occupations from simple (i.e., stationary condition with no intertrial variability and object manipulation) to hard (i.e., in-motion conditions with intertrial variability and object manipulation) levels based on their priorities identified via Canadian Occupational Performance Measure. All patients will be actively participating in at least three to four occupations. Therefore, all participants will receive the same amount of intervention. The therapists will keep a record of the extent of participation in each occupation using a visual analog scale during each session.

Moreover, feedback statements that have the potential to create a sense of responsibility (i.e., derived from international and national Delphi studies with renowned experts and patients) in patients will be provided to participants as knowledge of performance or knowledge of the result. These feedback statements will be positive or negative statements in relation to the individual or his/her family for prevention/symptom management and function improvement. These feedback statements (i.e., based on type, target, and purpose) will be presented to the patients throughout the intervention sessions. An expert panel was held to sort the feedback statements so that patients receive all forms of feedback in each session. Some examples of responsibility feedback are provided in Table 2.

This group will receive conventional interventions (see below) for 15 min in each session. They will receive occupation-based interventions with responsibility feedback for the remaining 45 to 75 min.

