### Data analysis

Data will be entered and analyzed using SPSS version 13. Each participant will have a registration number. All printed questionnaires and datasets will be stored in a secure locker and computer, respectively. Missing data will be handled by random coefficient analysis [68]. Intention-to-treat analysis will be performed for dropout participants during treatment sessions or follow-up assessments. Dropout participants will not be excluded from the sample size and data analysis. There will be no planned interim analyses and no planned stopping rules for this trial. The mean (standard deviation) or median (inter-quartile range) will be calculated for quantitative variables. For categorical variables, frequency (percentages) will be used. To check the normality of data, Shapiro-Wilk, graphical methods, and numerical indices will be used.

Quantitative demographic variables between the three groups will be compared using one-way ANOVA or Kruskal-Wallis tests. Chi-squared will be used for comparing the categorical variables between the groups. If there will be no significant difference between various outcome measures in the three groups at baseline, outcome measures will be analyzed using a 3 × 5 repeated measure analysis of variance with group (occupation-based interventions with responsibility feedback; occupation-based interventions without responsibility feedback; conventional) as between-subject factor and time (baseline, session 9, session 17, post-intervention, follow-up) as within-subject factor. A Tukey post hoc test will be performed for multiple comparisons. However, if a significant difference will be obtained for outcome measures in the three groups at baseline, a separate regression analysis will be done by considering group and baseline as covariates at each assessment point (i.e., session 9, session 17, post-intervention (week 13), follow-up (week 25)). The differences will be calculated via Kruskal-Wallis. All analyses will be considered significant with a 2-tailed *P* < 0.05.

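### The protocol article promises to find the proper dose from repeated assessments, but one fixed schedule for everyone cannot show whether fewer sessions would suffice

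*Protocol article*

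**What the plan says.** The statement of intent is in the protocol article under Data collection: "We will intend to discover the proper dose of intervention by multiple assessments during the treatment process". The sentence before it cites a review that expressed dose as sessions and weeks together (at least 8 sessions and at least 10 weeks).

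The rest of the article fixes the schedule:

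- Abstract, Methods: "All participants will receive intervention for 24 sessions during a period of 12 weeks (2 sessions per week").
- Interventions: "In each group, treatment sessions will be delivered two times a week", and "Each session will be approximately 60 to 90 min".
- Trial design: "Individuals will be assigned to each group in a ratio of 1:1:1". The three arms differ in type of intervention; none is defined by number of sessions.
- Data collection, on timing: "outcome measure evaluations at baseline, session 9, session 17, post-intervention (week 13), and follow-up (week 25").
- Data analysis: "outcome measures will be analyzed using a 3 × 5 repeated measure analysis of variance with group" and time as the factors. If the arms differ at baseline, a separate regression on group and baseline replaces it at each later visit. Neither model has a term for dose.

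**The concern.** To learn what dose is sufficient, a trial has to compare people who received different amounts, preferably by random assignment. Here the planned number of sessions at any visit is the same for everyone and is set by the calendar. The visits at sessions 9 and 17 give a time course under one schedule, which is a different quantity from a dose response.

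The risk lies in interpretation. If the arms differ at session 17 and the week 13 visit adds nothing significant, it would be easy to report that the earlier number of sessions was enough. The Discussion expects the findings to inform clinicians' decisions, so such a statement could be acted on. The trial would not have observed whether a benefit seen at session 9 or 17 lasts once treatment stops there.

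**Working it through.** **1. What the trial was sized for.** Inputs from Sample size calculation: f = 0.25, correlation among repeated measures 0.25, power 80%, type I error 5%. From Trial design and Data analysis: k = 3 groups, m = 5 visits. For the group-by-time interaction with sphericity assumed:

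- λ = N f² m / (1 − ρ) = 39 × 0.0625 × 5 / 0.75 = 16.25
- df = (k − 1)(m − 1) = 8 and (N − k)(m − 1) = 36 × 4 = 144
- power = 0.812

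This reproduces the stated 39. The between-groups test would need 66 and the within-subjects test 30. The trial is therefore sized for arms diverging over time, not for a dose question.

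**2. Sessions against time.** Assume the assessments labelled session 9 and session 17 come after 8 and 16 completed sessions. At two a week:

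| Visit | Sessions completed | Approximate week |
|---|---|---|
| Baseline | 0 | 0 |
| Session 9 | 8 | 4 |
| Session 17 | 16 | 8 |
| Post-intervention | 24 | 12 (assessed in week 13) |
| Follow-up | 24 | 25 |

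Over the first four visits the correlation of sessions with weeks is 1.00, or 0.998 with the last placed at week 13. If the assessments follow 9 and 17 completed sessions, the two remain tied in the same way.

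**3. Can a dose effect be estimated separately?** With visit as a factor, planned sessions = 8 × (session 9 visit) + 16 × (session 17 visit) + 24 × (post-intervention visit). This is an exact combination of columns already in the model:

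- four visits: 5 columns, rank 4
- with follow-up added: 6 columns, rank 5
- linear sessions and weeks, each crossed with group: 9 columns, rank 6

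The separate regressions do not help, because within one visit the planned number of sessions is constant. A larger sample changes none of this. Follow-up at week 25 does vary time at 24 sessions, but it measures retention after the full course, not the effect of a shorter one.

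**4. Illustration: how informative is a non-significant step?** Inputs: 39 / 3 = 13 per arm; correlation r = 0.25 from the article, with 0.5 and 0.7 as an assumed sensitivity range; a further between-arm gain of 0.5 SD between two visits, also assumed.

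SE of the two-arm difference in change = √(2(1 − r)) × √(2/13), in SD units. The 95% half-width uses t(24) = 2.064, and power comes from the noncentral t distribution, two-sided 5%.

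| r | SE | 95% half-width | Power for 0.5 SD |
|---|---|---|---|
| 0.25 | 0.480 | 0.99 | 0.17 |
| 0.5 | 0.392 | 0.81 | 0.23 |
| 0.7 | 0.304 | 0.63 | 0.35 |

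With all 15 per arm retained, power is 0.19 to 0.40 over the same range of r. A within-arm paired change of 0.5 SD (n = 13) has power 0.27 to 0.57. A between-arm gain of 1.0 SD (13 per arm) has power 0.52 to 0.88.

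**The case against.** Much of the case for the article is sound.

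- **Dose accumulates within each participant.** One can follow a participant through about 8, 16 and 24 sessions while treating everyone alike, so a uniform schedule does not by itself contradict the stated intent. A reader might infer a contradiction from "Therefore, all participants will receive the same amount of intervention". That sentence sits in the group A text and follows from the number of occupations each patient works on; it does not concern sessions across arms. It is not evidence for this point.
- **The article's notion of dose joins sessions and weeks.** On that notion the two intermediate visits do estimate between-arm effects after about 4 and 8 weeks at two sessions a week. This stands, but such an estimate still does not say what would follow if treatment ended there.
- **Randomisation protects the contrasts.** A reader might infer that every change between visits is confounded with retesting and disease course. Between-arm contrasts on a shared schedule remove what is common to all arms, so that inference holds only for changes within an arm.
- **Dose received will vary somewhat.** Sessions run 60 to 90 minutes, participants may stop early, and some records are kept each session. This variation is not randomised, is plausibly related to patients' condition and adherence, and has no analysis stated for it.
- **Dose is peripheral.** It does not appear in the study aim, the outcomes, the sample size or the analysis. That limits the weight of the point. It also shows that nothing in the plan supports the stated intent.

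**Conclusion.** The point holds in a limited form. The design can describe when the arms separate under the fixed schedule. It cannot separate number of sessions from elapsed weeks, and it cannot show whether fewer sessions would suffice, because nobody is assigned to stop earlier. This rests on the schedule and the randomised factor alone, so neither sample size nor a more detailed analysis plan would repair it.

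The 17% to 35% power range is an illustration that depends on the assumed 0.5 SD gain and range of correlations. Its complement, 65% to 83%, might be taken as the rate at which the trial would declare a false plateau. The article does not support that, since it nowhere says that a non-significant step will be read as a plateau, and a gain of 1.0 SD would be detected far more often. The illustration supports only the caution that a non-significant step is weak evidence that benefit has stopped growing.

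The primary between-arm comparison of participation satisfaction is unaffected. The change should be made, but the trial does not depend on it.

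**What to change.** In Data collection, replace the dose-discovery sentence with a statement to this effect: the assessments at sessions 9 and 17 describe the time course of between-arm differences under the fixed schedule, reported with 95% confidence intervals; because planned sessions and elapsed time move together and no participant is assigned to a shorter course, no conclusion about the sufficient number of sessions will be drawn.

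The cost is wording and the loss of one secondary claim. Visits, data collected, sample size and the primary comparison stay as they are.

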**Table 1 Tab1:**
[figure not shown]
Schedule for treatment and outcome measures

Group A: occupation-based interventions with responsibility feedback. Group B: occupation-based interventions without responsibility feedback. Group C: conventional interventions

*PD* Parkinson’s disease, *ADL* Activities of daily living, *IADL* Instrumental ADL

### Inclusion and exclusion criteria

The inclusion criteria will be (a) diagnosis of idiopathic PD based on the UK Brain Bank criteria [42], (b) absence of impulsive-compulsive disorder based on interviews by the neurologist and published criteria [43–45], (c) Hoehn and Yahr stages of I to III [46], (d) aged between 35 and 85, (e) acceptable cognitive function (a score of > 24 on Montreal Cognitive Assessment [47]), and (e) able to read and write in Persian for completing self-report questionnaires. The exclusion criteria will be (a) atypical parkinsonian syndromes [48]; (b) other existing neurological disorders, such as stroke; and (c) juvenile PD.

### Randomization and blinding

After obtaining consent and baseline data, an independent researcher who will not be involved in assessments will allocate the participants to each group. Participants will be randomly assigned to each group using a sequence generated by http://www.randomizer.org. For determining concealment, unique codes will be written on envelopes which contain group specifications. The assessor will be blind to the allocation of participants in groups and will enter data in the OT clinic. We do not anticipate any requirement for unblinding but if required, the trial steering committee (i.e., chief investigators and clinical project manager) will have access to the group allocations and any unblinding will be reported. Assessments will be conducted before allocation. Moreover, patients will not know which intervention they are receiving.

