### Sample size calculation

The sample size was estimated using the G-Power software with Cohen’s *f* standardized effect size of 0.25, correlation among repeated measures of 0.25, power of 80%, and first type error of 5% based on the primary outcome measure (i.e., Utrecht Scale for Evaluation of Rehabilitation-Participation Satisfaction) [49]. The total sample size was calculated as 39 subjects which increased to 45 subjects by assuming a 15% dropout rate. In order to assure the sufficiency of the sample size, power calculation will be performed again at the end of the trial.

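### Hoehn and Yahr stage is known before allocation but is neither a described stratification factor nor a term in either outcome model, which costs precision and credibility with about 15 patients per arm

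*Protocol article*

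**What the plan says.** Under Inclusion and exclusion criteria, patients at "Hoehn and Yahr stages of I to III" are eligible, so stage is established for everyone before allocation. Under Trial design, "Individuals will be assigned to each group in a ratio of 1:1:1". Under Randomization and blinding, the method is given as "Participants will be randomly assigned to each group using a sequence generated by http://www.randomizer.org", and for concealment "unique codes will be written on envelopes which contain group specifications". No stratification factor is described.

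The Data analysis section lists the terms of the outcome models. If the arms do not differ significantly on the outcomes at baseline, the model is a 3 × 5 repeated-measures ANOVA with group and time, where baseline is one of the five time levels. If they do differ, "a separate regression analysis will be done by considering group and baseline as covariates at each assessment point". Stage is in neither. Quantitative demographic variables and categorical variables are compared between arms, but no adjustment follows from that comparison.

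**The concern.** Stage is a recorded measure of severity in a small three-arm trial, and the plan as described uses it neither in allocation nor in analysis. With about 15 patients per arm, chance can leave one arm with clearly more stage III patients than another. If stage affects how participation satisfaction changes up to week 25, such a gap becomes part of the observed arm contrast, and the stage-related variation stays in the error term. Readers who see the imbalance in the baseline table would then have no pre-specified adjusted result, and an adjustment chosen after the data are seen carries less weight.

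The absence of stage from the models does not rest on silence, because the article states the terms of both branches.

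**Working it through.** **1. The plan's sample size, and the test it powers.** Inputs from Sample size calculation: "Cohen’s *f* standardized effect size of 0.25", "correlation among repeated measures of 0.25", power 80%, alpha 5%. With k = 3 arms, m = 5 time points and sphericity (epsilon = 1), the group-by-time test has noncentrality f²·N·m/(1 − ρ) = 0.0625 × 39 × 5 / 0.75 = 16.25, with (k − 1)(m − 1) = 8 and (N − k)(m − 1) = 144 degrees of freedom. Power is 0.812, so N = 39 is reproduced, and 39 × 1.15 = 44.85 gives 45. A test of the group main effect would need 66. The powered test is therefore group-by-time.

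**2. How often stage is unbalanced with equal arms.** The article gives no stage mix, so the number K of stage III patients among 45 is an assumption. With 15 per arm, the probability of a, b and c stage III patients in the three arms is C(15,a)·C(15,b)·C(15,c)/C(45,K), where a + b + c = K. Summing this exactly:

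| Stage III among 45 (assumed) | Some pair of arms differs by ≥ 4 | Groups A and B differ by ≥ 4 |
|---|---|---|
| 9 | 25% | 11% |
| 15 | 36% | 18% |
| 22 | 42% | 21% |

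**3. What each planned test does with such a gap.**
- Group-by-time test: a stage effect that is the same at all five time points is removed with the patient's mean level. Only a stage effect on the course remains.
- Group main effect: a stage difference in level remains.
- Per-visit regression: the baseline score absorbs part of a level effect. A stage effect on later change remains.

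**4. Size of the shift.** Suppose stage III alters change from baseline by 0.3 to 0.8 SD (assumption). A gap of 4 in 15 then moves an arm contrast by 4/15 × 0.3 = 0.08 SD to 4/15 × 0.8 = 0.21 SD. Two yardsticks:
- f = 0.25 with three equally spaced means corresponds to an extreme-arm difference of 0.25 × 2 × √1.5 = 0.61 SD. This is only a rough guide, since the plan's f refers to the interaction.
- With ρ = 0.25, change from baseline has variance 2 × (1 − 0.25) = 1.5 SD². The standard error of an arm contrast in change is √(2 × 1.5/15) = 0.45 SD. The shift is about one fifth to one half of that.

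**5. Price and gain of the covariate.** At N = 45, error degrees of freedom for the interaction test fall from (45 − 3) × 4 = 168 to (45 − 4) × 4 = 164. With noncentrality 0.0625 × 45 × 5 / 0.75 = 18.75, power stays at 0.88 if stage is unrelated to the outcome. In simulation, adding stage cost under half a percentage point of power when it was unrelated to the outcome, and gained about 1 to 6 points when it shifted the outcome by 0.5 to 1.0 SD (assumption).

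**The case against.** Randomisation without stratification is valid. Chance imbalance is part of the sampling error that the standard error already describes, so it neither biases the test nor inflates alpha. This stands, and the point claims only a loss of precision and credibility.

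The planned models already give some protection, as step 3 shows. This also stands, and a reader who infers that stage differences go wholly uncorrected goes too far. The protection is partial, however. The regression is used only after a significant baseline difference, and at N = 45 a one-way test detects f = 0.25 with power of only 0.28 (noncentrality 0.0625 × 45 = 2.81 on 2 and 42 degrees of freedom).

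A reader might also infer that the list was unrestricted, so that arm sizes drift. The article does not say so. A 1:1:1 ratio and coded envelopes fit a list balanced at 15/15/15 just as well, and a condensed article may leave block details to the full protocol. Even if the list were unrestricted, the loss would be small: for a between-group test, power falls from 0.624 at 15/15/15 to 0.611 at 12/15/18 or 0.589 at 10/15/20.

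Lastly, the documents do not show that stage affects the course. Occupations are graded to the patient's functional level, not to stage. That stands, so the effect sizes above are assumptions. Choosing stage over age or disease duration is a judgement; its merit is that eligibility guarantees a value for every patient.

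**Conclusion.** The point holds in a limited form. Stage is known before allocation, is not a described stratification factor, and is absent from both stated outcome models. With equal arms, a gap of 4 or more stage III patients between some pair of arms occurs in about 36% of trials if one third are stage III, and in 25% to 42% if 9 to 22 of the 45 are. Under an assumed stage effect on change of 0.3 to 0.8 SD, such a gap moves a contrast by 0.08 to 0.21 SD. What is left unaddressed is a stage effect on the course to week 25, and a stage difference in level in the group main effect. The documents do not support a claim of bias, of inflated type I error, or of unequal arms from unrestricted randomisation. The change is worth making because it is cheap, even though the gain may be small.

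**What to change.** Before unblinded analysis, pre-specify stage (I-II versus III) as a covariate in every outcome model:
- In the repeated-measures model, include stage and stage-by-time. A stage main effect alone would leave the group-by-time test unchanged in complete data. A between-subject covariate in a standard repeated-measures GLM normally carries the time interaction, but the plan should say so.
- In the per-visit regressions, add stage as a main effect next to group and baseline.

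The cost is one or two sentences in the analysis section, one degree of freedom, and four more for stage-by-time. No new data are needed. If stage is weakly prognostic, the gain is slight.

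No new allocation list is proposed. Trial status reports recruitment from September 2022 and last assessments expected by June 2023. With follow-up at week 25, the last allocation would fall around January 2023, before the article appeared in September 2023, so recruitment has probably ended.
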